# Project T-SHARP: study protocol for a multi-site randomized controlled trial of tele-harm reduction for people with HIV who inject drugs

**DOI:** 10.1186/s13063-023-07074-w

**Published:** 2023-02-07

**Keywords:** HIV, People who inject drugs, Harm reduction, Telehealth, Syringe services program

## Abstract

**Background:**

The resurgence of HIV outbreaks and rising prevalence among people who inject drugs (PWID) remain exigent obstacles to Ending the HIV Epidemic in the USA. Adapting a low threshold, comprehensive treatment model for PWID with HIV can leverage syringe services programs (SSPs) to increase availability and accessibility of antiretrovirals (ART), medications for opioid use disorder (MOUD), and hepatitis C cure. We developed *Tele-Harm Reduction*, a telehealth-enhanced, harm reduction intervention delivered within an SSP venue.

**Methods:**

The T-SHARP trial is an open-label, multi-site, randomized controlled superiority trial with two parallel treatment arms. Participants (*n*=240) recruited from SSPs in Miami, Ft. Lauderdale, and Tampa, Florida, who are PWID with uncontrolled HIV (i.e., HIV RNA>200) will be randomized to *Tele-Harm Reduction* or off-site linkage to HIV care. The primary objective is to compare the efficacy of *Tele-Harm Reduction* for initiation of ART at SSPs vs. off-site linkage to an HIV clinic with respect to viral suppression across follow-up (suppression at 3, 6, and 12 months post randomization). Participants with HIV RNA<200 copies/ml will be considered virally suppressed. The primary trial outcome is time-averaged HIV viral suppression (HIV RNA <200 copies/ml) over 3-, 6-, and 12-month follow-up. Secondary outcomes include initiation of MOUD measured by urine drug screen and HCV cure, defined as achieving 12-week sustained virologic response (negative HCV RNA at 12 weeks post treatment completion). A cost-effectiveness analysis will be performed.

**Discussion:**

The T-SHARP Trial will be the first to our knowledge to test the efficacy of an innovative telehealth intervention with PWID with uncontrolled HIV delivered via an SSP to support HIV viral suppression. *Tele-Harm Reduction* is further facilitated by a peer to support adherence and bridge the digital divide. This innovative, flipped healthcare model sets aside the traditional healthcare system, reduces multi-level barriers to care, and meets PWID where they are. The T-SHARP trial is a pragmatic clinical trial that seeks to transform the way that PWID access HIV care and improve HIV clinical outcomes.

**Trial registration:**

ClinicalTrials.gov NCT05208697. Trial registry name: Tele-Harm Reduction. Registration date: January 26, 2022.

## Introduction

### Background and rationale {6a}

The recent decade’s resurgence of HIV outbreaks and rising prevalence among people who inject drugs (PWID) remain exigent obstacles to Ending the HIV Epidemic (EHE) [1–5]. PWID account for a substantial portion of new HIV infections in the USA, which increased 8.7% between 2015 and 2019 [2, 6, 7]. Historically, PWID experience disproportionately higher HIV burden associated with sexual and injection behavior, including sexual coercion and sharing of drug preparation equipment [8, 9]. More than half (55.2%) of individuals engaging in injection drug use have hepatitis C virus (HCV) [10–12]. Their suboptimal health outcomes are often perpetuated by structural harms, including limited resources, the ongoing overdose crisis, difficulty accessing treatment for substance use, and unstable housing [4, 10, 13]. A recent drop-in HIV clinic intervention among a cohort of housing unstable individuals with substance use disorder (SUD) and uncontrolled HIV in San Francisco reported only 44% viral suppression at 12 months [14]. Furthermore, PWID living with HIV face intersecting stigmas that affect adherence to care in the traditional healthcare setting and to antiretroviral therapy (ART), and subsequently viral suppression [15–17].

The COVID-19 pandemic further complicated access to care for PWID, ushering in a sharp rise in opioid overdoses [18]. In-person harm reduction strategies were difficult to implement during the first year of the pandemic, with 43% of syringe services programs (SSPs) initially reporting a decrease in the availability of treatment services, and a quarter having to shut down entirely [19, 20]. In post-COVID adaptation of SSP programming, HCV cure, medications for opioid use disorder (MOUD), and HIV viral suppression in the high incidence group of PWID are urgently needed.

Highlighted as a cornerstone intervention in the four pillars of the EHE initiative, SSPs are low-barrier community programs uniquely positioned to provide cost-effective harm reduction services while protecting against infectious disease transmission [21–23]. Wraparound health promotion services at SSPs include the provision of sterile injection equipment, naloxone provision, wound care for treatment of skin and soft tissue infections, and HIV and hepatitis C screening, and many offer pre-exposure prophylaxis (PrEP), ART, and MOUD [23, 24].

Onsite medication treatment at SSPs has improved pharmacologic adherence and subsequently health outcomes for PWID [25, 26]. Variations of onsite HCV treatment colocated at SSPs may bundle testing, phlebotomy, and medication distribution. These studies report high rates of uptake and more than 89% of patients achieving sustained virologic response [26, 27]. One low-barrier onsite buprenorphine treatment program reported one-third of SSP participants continuing MOUD for 180 days or more [25]. Treatment retention among PWID with HIV on MOUD is significant compared to those not on MOUD, as one non-SSP systematic review and meta-analysis found that MOUD was associated with a 69% increase in ART initiation, 2-fold increase in adherence, and 45% increase in odds of HIV viral suppression [28].

Telehealth harnessed during the COVID-19 pandemic improved the treatment gap for people with HIV who use drugs, decreasing barriers of transportation and expanding outreach to remote communities, especially those experiencing homelessness [29, 30]. For people with HIV, telehealth helped providers overcome many of the factors described as barriers to care, including fear of judgement in face-to-face consultations and concerns of privacy and confidentiality [31]. Emergency regulatory changes waived the in-person clinician visit for buprenorphine prescribing, allowing for low-barrier telehealth-enhanced harm reduction interventions to be delivered to sites often frequented by PWID, including SSPs [29]. One SSP-centered telehealth model [32] offered successful co-treatment for HIV, substance use disorder, and HCV with similar rates of SVR as treatment colocated on site at an SSP [26]. However, currently no trials exist that focused on achieving viral suppression with PWID with HIV by employing a harm reduction approach in the setting of an SSP.

Adapting a low threshold, comprehensive treatment/harm reduction model for PWID with HIV can leverage trusted SSPs to increase availability and accessibility of ART, MOUD, and HCV cure. We developed *Tele-Harm Reduction* (THR), a telehealth-enhanced, harm reduction intervention delivered by an SSP that already has partnerships with the PWID community including those experiencing homelessness [33, 34]. The overall goal of this project is to compare the efficacy of the *THR* intervention in achieving HIV viral suppression among PWID with uncontrolled HIV infection in accessing services at an SSP compared to current standard of care (i.e., off-site linkage to HIV care).

### Objectives {7}

The primary objective is to compare the efficacy of *THR* for initiation of ART at SSPs vs. off-site linkage to an HIV clinic with respect to viral suppression across follow-up (suppression at 3, 6, and 12 months post randomization). Participants with HIV RNA<200 copies/ml will be considered virally suppressed.

The primary hypothesis is that *THR* will be superior to off-site linkage in achieving HIV RNA<200 copies/ml measured by the proportion of participants virally suppressed across follow-up (time-averaged viral suppression).

The secondary objectives are to measure differences between study arms in MOUD initiation and HCV cure. Participants in the *THR* arm will have enhanced access to medical and mental health clinician visits via a telehealth platform and remote phlebotomy in addition to medication management (e.g., storage in pill lockers at SSP, weekly delivery) and appointment reminders. Participants assigned to the off-site linkage arm will be linked to a traditional Ryan White clinic by SSP staff as is currently the standard of care. MOUD initiation is measured by buprenorphine, naltrexone, or methadone on urine drug screen (UDS). HCV cure (i.e., HCV RNA undetectable) is defined as sustained virologic response after completing direct acting antivirals (DAA), i.e., SVR12. Mediating effects of the intervention on injection risk behaviors (i.e., syringe reuse and syringe sharing) will also be assessed.

For the economic analysis, *THR* is expected to have a higher cost but be more effective in increasing uptake of ART, MOUD, and DAA, as well as HIV viral suppression, MOUD retention, and HCV cure among PWID participants. Incremental cost-effectiveness ratios (ICERs) will be calculated to report the additional cost per unit of desired outcome (e.g., increased ART and MOUD initiation) in the *THR* vs. off-site linkage to HIV care arms.

### Trial design {8}

The T-SHARP trial is a non-blinded, multi-site, randomized controlled superiority trial with two parallel treatment arms. Participants who are PWID with uncontrolled HIV (i.e., HIV RNA>200) will be randomized to *THR* or off-site linkage to HIV care in a 1:1 block randomization. A cost-effectiveness analysis will be performed. The study protocol (version 1.0) follows the Standard Protocol Items: Recommendations for Interventional Trials (SPIRIT) Statement.

## Methods: participants, interventions and outcomes

### Study setting {9}

Miami, Ft. Lauderdale, and Tampa are optimal cities for studying *THR* in the context of SSPs. IDEA Miami and IDEA Tampa are both housed within academic medical centers (University of Miami, University of South Florida) in partnership with safety-net hospitals (Jackson Health System, Tampa General Hospital). In consultation with our study sponsor, a third site was funded in September 2022 for the T-SHARP trial, also in an EHE jurisdiction, at the Federally Qualified Health Center-based SSP, the SPOT located in Ft. Lauderdale, Florida.

### Eligibility criteria {10}

Eligibility criteria include the following: (1) age 18 or older; (2) able to speak English; (3) enrolled in IDEA Miami, IDEA Tampa, or the SPOT SSPs; (4) injection drug use in past 12 months by self-report; (5) willing and able to sign informed consent, provide locator information and medical records release; (6) testing reactive for HIV by rapid test; and (7) HIV RNA>200 copies/ml as determined by on-site labs or abstracted medical records (result within 3 months of randomization date). Of note, pregnant people are eligible for enrollment in this trial.

Exclusion criteria include the following: (1) testing HIV negative via rapid test; (2) receipt of THR intervention in the past 6 months; (3) inability to provide informed consent; (4) planning to leave the area within 12 months; (5) principal or site investigator discretion; (6) currently in prison or jail; and (7) enrollment in NIDA Clinical Trials Network CTN 121. Investigator discretion could include serious medical, psychiatric, or co-occurring substance use disorder that acutely requires a higher or different level of care including the following: (1) disabling or terminal medical illness (e.g., decompensated heart failure, cirrhosis, or end-stage liver disease); (2) severe, untreated, or inadequately treated psychiatric condition (e.g., active psychosis); (3) in need of medical detox for severe alcohol, benzodiazepine, or other depressant or sedative hypnotic use; (4) suicidal intent or plan; or (5) homicidal ideation.

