### Additional consent provisions for collection and use of participant data and biological specimens {26b}

We will request consent for review of participants’ medical records, and for the collection of blood samples to assess HIV viral load. In detail, study participants will be administered full informed consent in English. Pre-screening consists of confirming that the participant is an SSP client, has a new anonymous reactive HIV test, or is known to have HIV and is out of care or non-adherent. Pre-screening is documented in the pre-screening log. If preliminary criteria are met, participants will complete the screening informed consent process including medical record release and then phlebotomy for HIV RNA. Medical record abstraction may be used to determine immediate eligibility. Consent for screening will be obtained by study staff using an IRB-approved written consent form. For those who meet eligibility criteria and would like to enter the study, informed consent will be obtained by study staff using an IRB-approved written consent form. All participants will be required to sign the medical record release form. All participants will be required to provide locator information including phone number, email, social media accounts (e.g., Facebook, Instagram), and friend/family contact information. Participants will receive a copy of all consent documents.

No additional studies are planned at this time.

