### Recruitment {15}

Participants will be recruited from three SSPs by our racially and ethnically diverse staff that includes peers. Recruitment will occur by referral during routine HIV/HCV screening that is offered at the SSP every 3 months. SSP staff will refer individuals with reactive results or known HIV infection. Flyers will be posted at the SSP and on social media accounts. We will also recruit via referrals from participants in the trial, and from clinicians caring for PWID in the hospital. Interested participants will meet with the peer or other study staff for a description of study activities, opportunities, and alternatives. Interested participants will sign the screening informed consent form to determine eligibility.

It is anticipated that throughout the recruitment period (months 18–48), routine HIV screenings and active and passive referrals will facilitate identification of 300 participants with HIV. Of these, we expect 80% to be eligible for randomization. We plan to use a locator form that we have used in other NIDA Clinical Trials Network studies that includes friend and family contacts, hangout spots, and social media accounts, in addition to phone and email.

For completing the screening process including quantitative assessment and laboratory analysis, participants will receive $40. Baseline data will be collected after main study informed consent, and participants will receive $50 per laboratory assessment (0, 3, 6, 12 months) and $50 per quantitative assessment (0, 6, 12 months) in both arms. Additionally, enrolled participants may refer up to 4 individuals to the study and receive $50 each if randomized. Total possible compensation is $590.

In anticipation of recruitment challenges, the study team has been awarded an administrative supplement to add a third trial site at the SPOT in Ft. Lauderdale, Florida, a federally qualified health center-based SSP. The current IRB-approved protocol has not been updated to include 3 sites at the time of publication.

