## Data collection and management

### Plans for assessment and collection of outcomes {18a}

Data collection is planned at screening, baseline, and at 3-, 6- and 12-month follow-up assessments. Quantitative behavioral questionnaires will be available in English and completed in REDCap under multi-factor authentication at UM. Measures will be included from NIDA’s Data Harmonization projects, particularly NIDA’s Seek Test Treat and Retain for Vulnerable Populations data consortium. Table 1 describes the battery of quantitative assessments planned.

Laboratory assessments will include indicated laboratories in PWID. At screening, these will include HIV RNA to determine eligibility as well as T cell subsets, HCV RNA, HBsAg, HBsAb, anti-HAV, RPR, and 3-site gonorrhea and chlamydia screening. Additional laboratory assessments occur at 0, 3, 6, and 12 months. HIV RNA is measured to confirm primary outcome at 3, 6, and 12 months. HCV RNA and UDS are measured to confirm secondary outcome measures in both arms.

For the cost and cost-effectiveness analyses, we will perform an economic evaluation of *THR* versus off-site linkage to HIV care. We will look at the cost to achieve a unit of effectiveness as defined by the main study and, to the extent possible, will look at this from different perspectives (healthcare, societal). For cost data, we will create custom resource trackers based on the DATCAP method [40]. DATCAP was designed as a program-level costing instrument for standard modalities of SUD treatment.

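### Entry on an HIV RNA up to 3 months old, with no rule for a newer suppressed result, can admit some people already suppressed and dilute the comparison

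*Protocol article*

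**What the plan says.** Trial design {8} of the Protocol article states the population: "Participants who are PWID with uncontrolled HIV (i.e., HIV RNA>200) will be randomized". Inclusion criterion 7 in Eligibility criteria {10} puts this into practice as "HIV RNA>200 copies/ml as determined by on-site labs or abstracted medical records (result within 3 months of randomization date"). The time limit can be read as covering on-site results as well as abstracted ones.

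The section on additional consent provisions {26b} describes the route to entry. Pre-screening confirms that the person is a client who "has a new anonymous reactive HIV test, or is known to have HIV and is out of care or non-adherent". Then "participants will complete the screening informed consent process including medical record release and then phlebotomy for HIV RNA". The same section adds: "Medical record abstraction may be used to determine immediate eligibility".

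Recruitment {15} names several referral sources, among them referrals "from clinicians caring for PWID in the hospital". The section on concomitant care {11d} leaves participants free to use other HIV services.

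Outcomes {12} defines the primary outcome as a state, HIV RNA below 200 copies/ml, averaged over months 3, 6 and 12. The primary GEE in section {20a} compares post-baseline measurements and names recruitment city as the model covariate.

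**The concern.** The outcome is a state at follow-up, not a change from entry. A person whose viral load fell below 200 between the qualifying sample and randomisation therefore meets the success definition before the assigned arm has done anything. The permitted look-back of 3 months equals the time to the first outcome visit, so the plan itself treats 3 months as long enough for suppression to be possible.

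One route is plausible from the text. A person has a value above 200 on a hospital admission, resumes treatment, is referred by a hospital clinician, and is later randomised on the admission value. Such entrants would tend to raise the suppression rate in both arms and shrink the difference. They would also move the analysed sample away from the population named in the objective. Recruitment {15} already anticipates difficulty reaching the target, so there is little spare sample size to absorb the loss.

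**Working it through.** **Step 1. Does any text close the route?**

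- Criterion 7 sets an age limit on the value but does not require non-suppression at randomisation.
- Section {26b} lets the record establish eligibility immediately, which implies that randomisation may precede a fresh laboratory result.
- Section {18a} says of HIV RNA: "At screening, these will include HIV RNA to determine eligibility". No text says what happens if that result is below 200 while the record is above 200.
- The out-of-care or non-adherent condition belongs to pre-screening and is not repeated among the eligibility criteria. It describes the person on that day, and treatment can start between then and randomisation.

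The route is narrowed but open.

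**Step 2. Reproduce the plan's figure.**

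Inputs from Sample size {14}: N=240 (120 per arm), alpha 0.05, power 0.80, three visits, within-subject correlation ρ from 0.10 to 0.80, minimum detectable difference 15 points. Sidedness is not stated; two-sided is assumed. The control rate P0 is taken as 50%, near which the plan says power is lowest.

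For m=3 visits with exchangeable correlation, the variance factor is (1+(m−1)ρ)/m. At ρ=0.5 it is (1+2×0.5)/3 = 0.667, so each arm counts as 120/0.667 = 180 independent observations. The minimum detectable difference is 11.3 points at ρ=0.1, 14.6 at 0.5, 15.3 at 0.6 and 16.5 at 0.8. The stated 15 points reproduces at ρ of about 0.5 to 0.6.

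**Step 3. Dilution.**

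Let f be the share already suppressed at randomisation, equal in both arms on average, and d the treatment effect in them. The observed difference is 15(1−f) + f·d. The documents give neither f nor d, so both are assumptions. With d=0, and starting from exactly 80% power (1.960+0.842 = 2.802), power = Φ(2.802(1−f) − 1.960).

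| f | participants of 240 | difference (points) | power |
|---|---|---|---|
| 0 | 0 | 15.0 | 80% |
| 5% | 12 | 14.25 | 76% |
| 10% | 24 | 13.5 | 71% |
| 20% | 48 | 12.0 | 61% |

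**Step 4. Cross-check with explicit proportions.**

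Take P0=50%, 65% under the intervention, ρ=0.5, and 90% of the already suppressed remaining below 200 in either arm. The control rate is 0.9f + 0.50(1−f) and the intervention rate is 0.9f + 0.65(1−f).

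At f=10% these are 0.540 and 0.675. With n=180, the pooled standard error is √(2×0.6075×0.3925/180) = 0.0515 and the unpooled one is √((0.540×0.460+0.675×0.325)/180) = 0.0510. Power is Φ((0.135−1.960×0.0515)/0.0510) = Φ(0.67), about 75%.

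| f | power, ρ=0.5 | power, ρ=0.8 | N for 80% power, ρ=0.5 |
|---|---|---|---|
| 0 | 82% | 72% | 228 |
| 5% | 79% | 68% | 248 |
| 10% | 75% | 63% | 274 |
| 20% | 66% | 55% | 334 |

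**Step 5. Relax the zero-effect assumption.**

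If the already suppressed gained half the effect (d=7.5) and f=20%, the difference is 0.8×15 + 0.2×7.5 = 13.5 points. That is the f=10% row of Step 3, or 71% power.

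**The case against.** The strongest reply is that the plan already has safeguards. Known-positive clients are pre-screened as out of care or non-adherent, and someone suppressed after resuming treatment would usually be neither. An investigator approves each randomisation. Screening includes phlebotomy for HIV RNA. The trial describes itself as pragmatic, and criterion 7 can be read as its working definition of uncontrolled HIV. Most of this stands, and it means the share affected may be small. It does not settle which value governs when a record and a newer sample disagree.

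The size is also open to challenge. A recently suppressed person can rebound within 12 months and may benefit from adherence support, so zero effect is pessimistic. The 15 points is a minimum detectable difference, not an expected effect. Both points are right, and the power figures are illustrations only.

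A reader might infer three stronger things that the documents do not support:

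- **That such participants could never be identified afterwards.** The screening draw described in {26b} and {18a} could identify them, and nothing says that using a record cancels it.
- **That no HIV RNA is taken at month 0.** Section {18a} says "HIV RNA is measured to confirm primary outcome at 3, 6, and 12 months", but this concerns confirmation of the outcome. Laboratory assessments also occur at month 0, their content is not listed in the text, and the assessment table is not shown.
- **That the result is biased towards Tele-Harm Reduction.** Randomisation balances these entrants on average.

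Finally, the analysis plan is not shown and may already name a baseline viral-load covariate. Its absence from the article is not the fault here; the covariate is proposed as a remedy.

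**Conclusion.** The point holds in a limited form. The eligibility rule, as written, allows entry on a value up to 3 months old, and no text requires non-suppression at randomisation or gives precedence to a newer result below 200. Pre-screening reduces the number who could enter this way but cannot exclude them.

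The consequence is dilution and a looser fit to the stated population. At assumed shares of 5% to 20% with no treatment effect in those participants, power falls from 80% to about 76% to 61%. With explicit proportions (P0=50%, ρ=0.5) it falls from 82% to about 79% to 66%. These figures rest on an assumed share, an assumed effect in those people and a two-sided test. The true loss could be negligible.

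A reader might also conclude that people with a documented restart of ART after the qualifying sample should be excluded. The documents do not support going that far: it is a recruitment trade-off in a trial that already expects difficulty enrolling, and the problem can be handled by measurement and analysis.

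**What to change.** Keep the record route for immediate eligibility. For every participant, obtain an HIV RNA from the screening phlebotomy already described, or run it on the planned month-0 draw before the assigned arm starts. Randomisation need not wait for the result. State in the protocol that this is the baseline value for analysis, whichever value established eligibility.

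Include it in the primary GEE alongside site, as log10 HIV RNA or as below 200 yes/no, with the form fixed in advance. Pre-specify a supporting analysis restricted to participants confirmed above 200 on that sample. Because the sample precedes treatment, this subgroup keeps the randomised comparison. Report the number in each arm found below 200, so that readers can judge the dilution directly.

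The cost is at most one extra assay per participant on blood already being drawn, one covariate and one supporting analysis. No visit is added and no one becomes ineligible. The adjusted odds ratio is then conditional on baseline viral load, so the difference in proportions should be reported with it.
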